#### Control definitions

In the US, MX, and SE, controls will be selected based on the absence of lifetime ED symptoms as determined via the ED100K.v4 [2]. Controls must have a minimum lifetime adult BMI ≥ 18.55 and maximum lifetime BMI < 30 and no history of binge eating, compensatory behaviors, use of glucagon-like peptide-1 (GLP-1) receptor agonists, or atypical AN. They also cannot report a history of an ED in any first-degree relatives. For AU and NZ, controls will be selected from healthy donor samples in previously collected cohorts. In DK, control inclusion criteria will be the absence of lifetime AN, BN, or other ED diagnosis based on ICD-10 codes.

#### Recruitment

EDGI2 recruitment in US, MX, AU, NZ, and SE will be multi-faceted, targeting broad populations. Direct case recruitment will be conducted from clinics and treatment programs actively involved in the study in the US and MX. For MX, children/adolescents (15–17 years of age) will only be recruited from the study clinic (Comenzar de Nuevo). NZ and SE will not perform direct recruitment from treatment services; however, clinician networks in both public and private treatment services will be invited to advertise the study. Coordinated recruitment campaigns will be launched in traditional media, including press releases, television, and radio to raise awareness about EDGI2. An engaging social media presence will be further developed on Facebook, Instagram, Bluesky, LinkedIn, Reddit, Snapchat, YouTube, podcasts, and emerging platforms to reach people on platforms and applications where they are active online. To personalize and amplify recruitment efforts, US, AU, NZ, MX, and SE will engage in consultation with people familiar with EDs and other interested parties (e.g., friends, family, caregivers, support providers) to encourage participation as cases or controls. Outreach will prioritize spotlighting varying body sizes and populations affected by EDs.

Controls for US, MX, and SE will also be recruited through the traditional and social media campaigns, and through community events and universities. AU and NZ will not recruit new controls. DK cases and controls will be acquired from the Danish National Health Registry of all individuals born in DK between 1981–2008; new cases (not captured in EDGI [1] or ANGI [2]) will be individuals with first BN and/or AN register diagnoses between 2016-present. Each country conducting active recruitment will have a unique local EDGI2 website providing localized information, educational material, and resources.

### Procedure

#### Consent and pre-screen questionnaires

Slight procedural differences exist across countries. In general, potential participants are directed through a link on their site-specific websites or a QR-code to a prescreen capturing basic eligibility information including age and other items reflecting inclusion criteria. If they meet criteria on the prescreen, they are shown a country-specific consent. Consent and prescreen questionnaires are applied through REDCap in US, MX, AU, and NZ. In SE, consent is collected through digital identification linked to Swedish national identity numbers. In MX, parent/guardian consent and child assent are required for child/adolescent (ages 15–17) participation and are collected in person at the main study clinic and registered on REDCap.

NZ has tailored consent and data management procedures for participants identifying as Māori (Indigenous People of NZ) and/or Pacific Islands Peoples (Pasifika) to align with national guidelines for health research. This consent and data management process recognizes the interconnectedness of Māori and Pasifika participants across individuals and across time, while enabling participation in this important international research. Their phenotypic and genetic data will be shared internationally under controlled access after approval by a NZ specific data access committee. Additional detailed information is available by contacting the NZ principal investigators.

#### Self-report measures

Slight procedural differences exist across participating sites. Individuals who complete the prescreen and consent are then presented with the EDGI2 questionnaire battery. We describe the specific metrics below in the order in which they will be presented (Table 1). 

*Screening questionnaire.* Participants are first presented with the ED100K.v4 questionnaire to determine eligibility and case designation [2]. Participants who meet eligibility criteria are asked for contact information and sent a unique link via email for the core and additional questionnaires. Participants can save and exit questionnaires at any time and navigate back to the survey as desired. In SE, contact information will be given directly after consent.

**Table 1 Tab1:** EDGI2 Assessment Battery (US, MX, AU, NZ, SE)

Questionnaire Section		Assessments Included	Domains Captured	Completed by
**Screening Questionnaire**		ED100K.v4 [2]. (including Lifetime Version of the Nine Item ARFID Screener [L-NIAS] [5], and Lifetime Version of the Pica, ARFID, and Rumination Disorder Interview – ARFID – Questionnaire [L-PARDI-AR-Q] [6] (adapted for this study)	Lifetime history of AN, BN, BED, and ARFID	All
**Core Questionnaires**		PACE Questionnaire (Polygenic Risk of Anorexia Nervosa and its Clinical Expression) [9]	Physical and emotional responses to feelings of hunger and fullness	All
		7-Item Binge-Eating Disorder Screener (BEDS- 7) [10]	Current BED symptoms	Case only
		Eating Disorder Examination-Questionnaire (EDE-Qv6) [11]	Current ED symptoms	Case only
		NIAS [5]	Current ARFID symptoms	All
		Muscle Dysmorphic Disorder Inventory (MDDI) [12]	Current symptoms of muscle dysmorphia	All
		Drive for Muscularity Scale (DMS) [13]	Current drive for muscularity	All
		Food Security (adapted for this study)[14]	Current symptoms of food insecurity	All
**Additional Questionnaires**	**Health and Treatment History**	Health History (developed for this study)	History of mental health, neurodevelopmental, gastrointestinal, and other disorders	All
		Item assessing ED-related nicotine use (developed for this study)	Lifetime nicotine use for the purposes of weight and shape modification	All
		ED-related stimulant use (developed for this study)	Lifetime stimulant use for the purposes of weight and shape modification	All
		ED Treatment History (developed for this study)	ED treatment history including barriers to care, tailored to site/country	Case only
		Menstruation (developed for this study)	Menstrual history	Female or intersex participants only
	**Mental Health and Behavior**	Obsessive Compulsive Inventory-Revised (OCI-R) [15]	Current obsessive–compulsive disorder symptoms	All
		Autism Spectrum Quotient- 10 (AQ- 10) [16]	Current symptoms associated with autism spectrum disorder	All
		Adult ADHD Self-Report Scale (ASRS) [17]	Current symptoms associated with ADHD	All
		Generalized Anxiety Disorder Screener (GAD- 7) [18]	Current anxiety symptoms	All
		Patient Health Questionnaire- 9 (PHQ- 9) [19]	Current depression symptoms	All
	**Lifetime Mood**	Depression, Mania, and Anxiety Sections of the Genetic Links to Anxiety and Depression (GLAD) Battery [20]	Lifetime symptoms of depression, mania, and anxiety	All
	**Self-Violence**^a^	Adapted Suicidal Ideation and Suicide Plan Sections of the Self-Injurious Thoughts and Behaviors Interview (SITBI) [21]	Lifetime suicidal ideation and suicide planning	All
		Adapted Suicidal Behavior Section of the Diagnostic Interview for Genetic Studies version 3.0 (DIGS) 3.0 [22]	Lifetime suicidal behavior	All
		Single-Item Non-Suicidal Self-Injury (NSSI) Screen (adapted from [23])	History of NSSI (yes or no)	All
		Adapted Inventory of Statements About Self-Injury (ISAS) [24]	Lifetime motivations for engaging in NSSI	All
	**Substance Use**	Adapted Lifetime Version of Alcohol Use Disorders Identification Test (AUDIT) [25]	Lifetime alcohol use	All
		Heaviness of Smoking Questionnaire [26]	Lifetime assessment of smoking	All
		Heaviness of Vaping Questionnaire [26]	Lifetime assessment of vaping	All
		Adapted Lifetime Version of Drug Use Disorders Identification Test (DUDIT) [27]	Lifetime drug use	All
	**Life Events**	Life Events Checklist for DSM- 5 (LEC- 5) (Adapted from [28])	Life events and trauma history, and emotional and physical neglect/abuse during childhood	All
	**ED-QOL**	ED Quality of Life (ED-QOL) [29, 30]	ED-specific health-related quality of life	Case only
	**CET**	Compulsive Exercise Test (CET) [31]	Compulsive and driven exercise	All
	**Perfectionism**	Multidimensional Perfectionism Scale (MPS) [32]	Perfectionism	All
	**CDE for Adults**	DSM- 5 Level 1 Cross-Cutting Questionnaire [33]	Current mental health domains that are important across psychiatric diagnoses	All
		World Health Organisation Disability Assessment Schedule version 2.0 (WHODAS v2.0) [34]	Current difficulties due to health conditions	All adult participants
	**CDE for Youth**^b^	DSM- 5 Level 1 Cross-Cutting for Youth version 1[35]	Current mental health domains that are important across psychiatric diagnoses, altered for youth assessment	All child participants
		Revised Children’s Anxiety and Depression Scale- 25 version 1.0 (RCADS- 25 v1.0)[36]	Measurement of current anxiety and low mood in youth	All child participants

EDGI2 questionnaire battery ordered by questionnaire section. ‘Domains captured’ describes the phenotype level information elicited by the questionnaire, and ‘completed by’ identifies which participants fill out the questionnaire, all (cases and controls), cases only, or participants in specific demographic groups

^a^excluded in some countries

^b^MX only

*Core eating disorder questionnaires*. The core battery includes validated questionnaires to measure eating behaviors and ED symptomology (Table 1). The questionnaires comprehensively phenotype AN, BN, BED, and ARFID, as well as transdiagnostic ED symptoms such as weight and shape concern and binge-eating behavior. Questions capturing muscle dysmorphia and food insecurity have been added based on community feedback. We hope to include atypical AN in the future. Participants in US and NZ receive gift card compensation upon completing all screening and core questionnaires and returning their saliva sample; in MX and SE, participants complete all questionnaires and provide a sample prior to receiving incentives; and incentives are not provided in AU.

*Additional Questionnaires.* Additional questionnaires capture 10 domains across physical health, mental health, substance use, treatment experiences and access (adapted for each country), exercise, and quality of life (Table 1). These additional questionnaires capture critically relevant information that informs a deeper phenotypic analysis, while also maintaining a survey length that does not overburden the participant.

#### Site specific questionnaires

*Sweden*. The EDGI2 battery has been linguistically translated into Swedish and culturally adapted for SE. SE-specific questionnaires address the impact of ED on social relationships, work, income, and education; participants’ perceived reasons for ED development; and factors supporting recovery. An additional Substance Use Questionnaire captures “snus” use (Swedish oral nicotine pouches). In addition to ED-QOL, quality of life is captured by the EuroQol-5 Dimension 5-level version questionnaire (EQ- 5D- 5L) [37]. Individuals who score > 3 on the AQ questionnaire also complete the Comprehensive Autistic Trait Inventory [38].

*Mexico*. The EDGI2 battery has been linguistically translated into Spanish and culturally adapted for MX. *Screening questionnaire*. This is only used to determine eligibility in adults who participate outside of Comenzar de Nuevo. All participants complete the Core Questionnaires. Adult participants complete all additional questionnaires, including CDE for adults. Participants 15–17 years complete all additional questionnaires except Self-Violence and the DUDIT portion of the Substance Use questionnaire. They will also complete CDE for youth.

*Australia and New Zealand*. AU and NZ are administering all questionnaires in the EDGI2 battery excluding the Self-Violence section of the additional questionnaires. NZ and AU have made country-specific and cultural adjustments to the Health and Treatment section.

#### Bio-sampling

Following completion of the ED100K.v4 and provision of contact information, eligible participants are sent a saliva sample collection kit via courier or mail (US, AU, NZ, SE). This includes a welcome letter, the saliva sample collection kit, site-specific instructions, and a pre-paid return envelope addressed to the participant’s respective collection site. For in-patient participants enrolled through some independent centers (e.g., ACUTE Center for Eating Disorders and Severe Malnutrition, Denver, CO and Sanford Health, Fargo, ND) the saliva sample collection kit is given to participants by study staff at these sites and mailed directly to the University of North Carolina at Chapel Hill (UNC). For other clinics (e.g., Gaudiani clinic), participants are sent emails about the study, receive saliva kits at home, and return them to UNC via post. For participants in MX, the saliva sample will be collected by research staff at a clinic or community event. Samples will be shipped to UNC. Standard DNA extraction and plating will be conducted at UNC, Queensland Berghofer Medical Research Institute (QIMR), and Karolinska Institutet (KI). Median DNA yield is 4 μg/ml saliva and excess saliva will be stored at − 20 °C. For DK, bloodspots linked to the DK national health registries will be genotyped by the DK Statens Serum Institut.

NZ has procedures in place for participants who reside in NZ and endorse Māori and/or Pasifika ethnicity consistent with current New Zealand ethics and best practice guidelines for health research. AU will adhere to national standards for data storage, access, and governance for participants from Aboriginal and Torres Strait Islander communities.

## Analyses

Using the most comprehensive state-of-the-science statistical analysis pipeline at the time of analysis, all analyses align into three phases reflecting Aims 2–4: i) interrogating heterogeneity and underlying biology of EDs, ii) risk prediction and identification of resilience and protective factors, and iii) determining where in the body EDs “live.” Careful consideration has gone into harmonizing multi-site cohorts and local ethics restrictions. US, MX, AU, and NZ (non-Māori/Pasifika), raw data will be stored on the UNC computing cluster “longleaf.” DK, SE, and NZ-Māori/Pasifika raw data cannot be shared and will be analyzed by respective sites into sharable summary statistics.

### Statistical Analyses of Heterogeneity and Underlying Biology of EDs (Aim 2)

#### Primary analyses (Aim 2a)

##### Genotyping, quality control (QC), and Imputation

EDs will be analyzed separately. Standard genotyping, QC, and imputation will be performed for US, MX, AU, and NZ. The genotyping array selected will be optimized for ancestrally diverse cohorts and downstream imputation accuracy. The Rapid Imputation for Consortias Pipeline (RICOPILI) [39] PGC GWAS analysis pipeline will be implemented and includes four key stages. Following best practices for multi-ancestry data [40], samples will be divided into ancestry specific cohorts, quality control and association testing performed, and finally meta-analyzed. Specifically, PCAiR GENESIS [41] with 1000 Genomes (1000G) reference panel [42] will be used to assign ancestry supergroups, PC-Relate will be used for relatedness checking [43], and admixture and ancestry assignments will be confirmed using ADMIXTURE [44]. Next, for each ancestry-specific cohort, genotype-QC will be performed, including estimating missingness, sample heterozygosity, sex concordance, Hardy–Weinberg equilibrium (HWE), minor allele frequency (MAF), batch effects, and cryptic relatedness between samples. The third stage will be phasing and imputation via Meta-imputation [45] using a high-quality, diverse reference panel, such as TOPMed [46] and expanded 1000G [47], to optimize imputation [48]. The fourth stage will be within-ancestry post-imputation QC, where cohorts will be filtered for imputation quality, MAF, and batch.

Genotyping, QC, and imputation will be performed in parallel at KI for all SE samples using parallel procedures, with minor variations as required. All DK samples will be genotyped by the DK Statens Serum Institut based on whole-genome-amplified DNA (in triplicate) and SNP array genotypes. QC and imputation will be performed in parallel at the Aarhus site. For NZ, Māori and Pasifika samples will be genotyped within NZ, with data QC and imputation also performed locally using parallel procedures, to honor sample and data sovereignty requirements. AU will follow similar procedures for Indigenous populations.

##### GWAS

GWAS will be performed by ancestry groups for each primary ED diagnosis, component behaviors, and dimensional traits captured through the EDGI2 battery. Binary and continuous GWAS will include correction for relevant covariates including sex, age, and genotype-derived principal components (PC) to correct for population stratification. The number of appropriate PCs will be determined using PCAiR.

For each ED, ancestry-specific EDGI2 GWAS will be meta-analyzed using MR-MEGA [49]. Where possible EDGI2 cohorts will be meta-analyzed with PGC-ED GWAS summary statistics, and any other publicly available ED GWAS summary statistics. In total, meta-analyses are expected to yield ~ 80,000 cases and ~ 730,000 controls (case-specific breakdown: AN≈47,000; BN≈16,000; BED≈10,000, ARFID≈6,500). By the time of analysis, additional cases may be contributed from independent international sites. Significant GWAS loci will be identified through standard per-GWAS Bonferroni correction and a conditional false discovery rate (FDR) approach across GWAS to identify shared loci [50].

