**Methods:**

A total of 20,000 new participants (18,700 cases and 1,300 controls) will be ascertained from the United States (US), Mexico (MX), Australia (AU), Aotearoa New Zealand (NZ), Sweden (SE), and Denmark (DK). Comprehensive phenotyping and genotyping will be performed for participants in US, MX, AU, NZ, and SE using the EDGI2 questionnaire battery and participant saliva samples. In DK, case identification and genotyping will be through the National Patient Register and bloodspots archived near birth. Case–control and case-case genome-wide association studies will be conducted within EDGI2 and enhanced via meta-analysis with external data from the Eating Disorders Working Group of the Psychiatric Genomics Consortium (PGC-ED). Additional analyses will explore genetic correlations between eating disorders (EDs) and other psychiatric and metabolic traits, calculate polygenic risk scores (PRS), and leverage functional biology to evaluate clinical outcomes. Moreover, analyzing PRS for patient stratification and linking identified risk loci to clinically relevant phenotypes highlight the potential of EDGI2 for clinical translation.

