### Inclusion criteria

#### Case definitions

Participants from US, MX, AU, NZ, and SE will be selected based on self-reported lifetime Diagnostic and Statistical Manual of Mental Disorders-fifth edition (DSM- 5) criteria for AN, BN, BED, and/or ARFID via the ED100K.v4 ED online questionnaire, revised from the previous version (ED100K.v3) to include ARFID [2]. The ARFID portion contains items developed by the study team in addition to adapted, lifetime versions of the Nine Item ARFID Screen (NIAS) [5] and Pica, ARFID, and Rumination Disorder ARFID Questionnaire (PARDI-AR-Q) [6]. In MX, those recruited through the Comenzar de Nuevo clinic will be identified based on clinical diagnosis. In DK, cases of AN and BN will be identified using International Classification of Diseases – 10 th Revision (ICD-10) codes (F50.0, F50.1 for AN; F50.2, F50.3 for BN). DK will not include ARFID or BED as no ICD-10 codes exist for these disorders. SE will link participants to diagnostic records from the Swedish National Patient Register and Quality Register (Riksät) that have been validated through diagnostic interviews with acceptable reliability [7].

For US, MX, AU, NZ, and SE, longstanding and/or severe AN (restricting or binge/purge AN subtype) will be captured by the EDGI2 battery and include AN duration ≥ 5 years, lowest illness-related BMI ≤ 15, ≥ 3 treatment periods, and above age 20 at enrollment. Severe cases with rapid weight loss who attain very low body weights will also be included. DK will use the Anorexia Nervosa Register-based Severity Index (AN-RSI), which creates a systematic and weighted combination of age at onset, inpatient treatments, outpatient readmissions, treatment length, and illness duration [8]. Modifications to the AN-RSI definition may be made based on emerging research.

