#### Mendelian randomization

We will use bidirectional, two-sample MR to interrogate putative causal directions for metabolic and anthropometric traits with high *r*_*g*_ for AN. SNP instruments for MR testing of disorder pairs will be selected based on *p* < 5 × 10^–8^ and *p* < 5 × 10^–6^, balancing power and weak instrument bias [94]. Inverse variance weighting (IVW) [95] is the basic method, and additional standard test considerations include Steiger filtering [96] for pleiotropic SNPs, adjusting for overlap between GWAS with MRlap [97], and FDR. To further account for weak instrument, confounding, and pleiotropic bias, we apply MR-Egger [98], MR PARS [99], and debiased IVW [100] and MR-APSS [101].

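### Conditional FDR across GWAS that share participants: no overlap adjustment is stated, and shared loci would be over-called for strongly overlapping pairs

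*Protocol article*

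**What the plan says.** The GWAS section of the protocol article plans a GWAS "for each primary ED diagnosis, component behaviors, and dimensional traits captured through the EDGI2 battery". It gives two rules for declaring loci. Within a single GWAS, "Significant GWAS loci will be identified through standard per-GWAS Bonferroni correction". Across GWAS, it uses "a conditional false discovery rate (FDR) approach across GWAS to identify shared loci". No FDR cut-off is given, and the cited method is not described.

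Three other places bear on overlap:

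- Case definitions admits people who meet lifetime "criteria for AN, BN, BED, and/or ARFID", so one person may be a case in two disorder GWAS. Nothing assigns separate controls to each disorder.
- Table 1 gives most of the battery to all participants, so the same people supply many of the behaviour and trait GWAS.
- Mendelian randomization provides for "adjusting for overlap between GWAS with MRlap". No other analysis names an overlap adjustment.

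**The concern.** Conditional FDR looks at SNPs with small P values in one GWAS and asks whether small P values are over-represented in a second. It reads any excess as shared genetics. That reading needs independent sampling errors. When the same people enter both GWAS, the z-scores of SNPs with no effect on either trait are correlated, and the same excess appears with no shared locus behind it.

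This rule is the one that declares loci shared across disorders and symptoms. Followed literally for strongly overlapping pairs, it would report sampling noise as pleiotropy and carry it into the cross-disorder interpretation.

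**Working it through.** **1. Inputs from the article.** The Abstract states: "A total of 20,000 new participants (18,700 cases and 1,300 controls) will be ascertained". The GWAS section states: "meta-analyses are expected to yield ~ 80,000 cases and ~ 730,000 controls", split as AN 47,000, BN 16,000, BED 10,000 and ARFID 6,500. The split adds up: 47,000 + 16,000 + 10,000 + 6,500 = 79,500, against about 80,000.

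**2. Null correlation from overlap.** For two case-control GWAS with n cases, c controls and N = n + c, sharing s_c controls and s_n cases:

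r = [s_c √(n1n2/(c1c2)) + s_n √(c1c2/(n1n2))] / √(N1N2)

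If all controls are shared and no cases are, this reduces to r = √(n1n2/(N1N2)).

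*Meta-analysed disorders, all 730,000 controls shared, no shared cases:*
- AN-BN: √[(47,000 × 16,000)/(777,000 × 746,000)] = 0.036
- BED-ARFID: √[(10,000 × 6,500)/(740,000 × 736,500)] = 0.011
- The other four pairs lie between these.

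*Same, with shared cases (assumed).* For BED-ARFID with half of the smaller group shared, s_n = 3,250. The added term is 3,250 × 730,000/√(10,000 × 6,500) / √(740,000 × 736,500) = 0.40, so r = 0.41. Over all six pairs:
- 10% of the smaller case group shared: 0.06-0.10
- 25% shared: 0.11-0.21
- 50% shared: 0.20-0.41

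*EDGI2-only disorder pair, 6,000 and 4,000 cases (assumed split), all controls shared.* With 1,300 controls, √[(6,000 × 4,000)/(7,300 × 5,300)] = 0.79. The 1,300 are newly ascertained controls. AU and NZ draw controls from earlier cohorts of unstated size, so the total must be varied:

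| Shared controls | r |
|---|---|
| 1,300 | 0.79 |
| 3,000 | 0.62 |
| 5,000 | 0.49 |
| 10,000 | 0.33 |
| 20,000 | 0.20 |

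*Two traits in the same people:* r is roughly the phenotypic correlation, for which the article gives no figures.

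**3. What r does to the declared loci.** Simulation with 200,000 independent SNPs, 10 replicates and a cut-off of 0.05 (assumed). The empirical statistic is cFDR(p1|p2) = p1 × #{P2 ≤ p2} / #{P1 ≤ p1, P2 ≤ p2}. A locus is called shared when the larger of the two directions (conjunctional FDR) is below 0.05. Each range covers three assumed architectures that contain truly shared loci: 0.2% shared plus 1% specific to each trait, 1% shared plus 1% specific to each, and a weaker-effect version with 0.2% shared. The last column uses one direction only.

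| r | Shared calls that are not shared | One-direction calls that are false |
|---|---|---|
| 0 | 6-9% | 6-9% |
| 0.036 | 7-11% | 6-8% |
| 0.1 | 7-15% | 7-10% |
| 0.2 | 12-24% | 7-13% |
| 0.3 | 17-32% | 9-16% |
| 0.5 | 41-76% | 23-47% |
| 0.7 | 71-96% | 46-86% |
| 0.8 | 84-98% | 60-93% |

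With no true effects at all, shared calls per run averaged 0.5 at r = 0, 104 at r = 0.5 and 943 at r = 0.7. Separate runs with 400,000 SNPs and 0.2% truly shared gave 7% false shared calls at r = 0, 19% at 0.3, 50% at 0.5 and 86% at 0.7.

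**The case against.** **The article is condensed.** The step gets one clause and a citation. The cited method or the full plan may already handle overlap, so silence does not prove that overlap is ignored. This stands, and the point is therefore limited to the rule as written. It does not remove the point: the article specifies the method and the set of GWAS, and names an overlap adjustment for one other analysis only.

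**The main use is safe.** The conditional FDR sentence follows the meta-analysis with about 730,000 controls, where shared controls alone do no harm. The per-disorder counts sum to about the total, which suggests that each case may be counted under one diagnosis only. Nothing says that conditional FDR will be run on EDGI2-only disorder pairs. All of this stands for the disorder pairs. It does not cover "component behaviors, and dimensional traits captured through the EDGI2 battery", which are in the GWAS set and come from the same people.

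**The high figures rest on assumptions.** The value 0.79 needs 1,300 to be the whole shared control set, and 20,000 controls would give 0.20. No trait pair is shown to have a phenotypic correlation of 0.5. The simulated shares vary with architecture and with which statistic defines a shared locus. This stands, so only ranges are given.

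**Other analyses are robust.** Bonferroni loci are unaffected, and GSEM, which can model overlap, is already planned across disorders and symptoms. This limits the damage but does not correct loci declared by conditional FDR.

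A reader might infer that most shared loci in this study will be false. The documents do not support that: it would need null correlations of about 0.5 or more, which are possible for some pairs but not shown for any.

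**Conclusion.** The concern holds in limited form. As written, conditional FDR is applied across GWAS with shared participants, and no overlap handling is stated for that step.

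- **Meta-analysed disorders sharing only controls:** null correlation at most 0.04, essentially no harm.
- **Meta-analysed disorders that also share cases:** about 0.1-0.4 if 10-50% of the smaller case group is shared. False calls are inflated but generally not the majority.
- **EDGI2-only disorder pairs, if analysed this way:** about 0.2-0.8, depending on the unstated number of AU, NZ and DK controls.
- **Traits in the same participants:** roughly the phenotypic correlation, not given.

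The false share moves clearly above nominal at 0.2-0.3 and can pass one half at about 0.5. These sizes rest on assumed case splits, case overlap, SNP effects and a 0.05 cut-off. The direction of the error does not depend on them.

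**What to change.** State in the GWAS section how conditional FDR handles overlap:

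1. Within each ancestry group, estimate the cross-trait LDSC intercept for every disorder and trait pair. The LDSC step behind the planned GSEM can supply these. The Genetic Correlations section is not enough as written, because it pairs eating disorder traits with other traits. LDSC is also limited to within-ancestry comparisons, so the intercepts cannot be taken from the multi-ancestry MR-MEGA results.
2. Then either decorrelate each pair of z-scores before conditional FDR, or restrict conditional FDR to pairs with a near-zero intercept (bound fixed in advance) or non-overlapping samples, and analyse the remaining pairs in GSEM.

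The second option is safer where the intercept is large. Symmetric decorrelation mixes the two z-scores with off-diagonal weight [1/√(1+r) − 1/√(1−r)]/2. This is −0.10 at r = 0.2 and −0.30 at r = 0.5. A locus specific to one trait is then partly carried into the other statistic. For the bound, the table above shows 7-15% false at r = 0.1 and 12-24% at r = 0.2, which argues for 0.1 or lower.

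The cost is a short addition to the text and a little extra analysis, with no new data. Fewer shared loci are likely to be declared. Splitting into non-overlapping halves is the costly variant: with 1% of SNPs shared, it cut calls from about 175-945 to about 31-36 per run, with 4-7% false.
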